| Study name               | Mesenchymal stem cells for prophylaxis of chronic graft-versus-host disease during the early stage after haploidentical hematopoietic stem cell transplantation
An Open-label, Multicenter, Randomized Controlled Clinical Trial                                                                                                                                                                                                                                                                                                                                                                                                                      |
| Clinical stage           | Phase II clinical study                                                                                                                                                                                                                                                                                                                                                                                                                                                                                                                                                                                                                                  |
| Research design          | Multicenter, randomized, controlled                                                                                                                                                                                                                                                                                                                                                                                                                                                                                                                                                                                                                      |
| Research center          | Medical Center of Hematology, Xinqiao Hospital, Army Medical University
920th Hospital of Joint Logistics Support Force
The Affiliated Hospital of Guizhou Medical University
The General Hospital of Western Theater Command
The Third Xiangya Hospital of Central South University                                                                                                                                                                                                                                                                                                                                                         |
| Test purposes            | To explore the efficacy of umbilical cord-derived mesenchymal cells in preventing graft-versus-host disease (GVHD) after haploid-hematopoietic stem cell transplantation                                                                                                                                                                                                                                                                                                                                                                                                                                                                                 |
| Number of study cases    | 158 cases                                                                                                                                                                                                                                                                                                                                                                                                                                                                                                                                                                                                                                                |
| Inclusion criteria       | (1) Patients diagnosed with acute leukemia who underwent haploid hematopoietic stem cell transplantation;
(2) Gender is not limited, age 18-60 years old;
(3) KPS score > 60 points, estimated survival time > 3 months;
(4) Patients without serious systemic organ dysfunction (a. creatinine <1.5mg/dl; b. albumin $\geq$ 2; c. cardiac ejection index > 55%; d. hemoglobin > 9g/dL, bilirubin element <2.0mg/dl);
(5) The patient has no other contraindications for hematopoietic stem cell transplantation;
(6) Voluntary test, informed consent.                                                                                   |
| Exclusion criteria       | (1) Severe cardiac, renal or hepatic insufficiency;
(2) Combined with other malignant tumors who need treatment;
(3) There are clinical symptoms of cerebral dysfunction or severe psychiatric disease, unable to understand or comply with the research protocol;
(4) Patients who cannot guarantee the completion of the necessary treatment plan and follow-up observation;
(5) Patients with severe acute allergic reactions;
(6) Clinically uncontrolled active infection;
(7) Patients who are participating in other clinical trials;
(8) The investigator believes that other reasons are not suitable for clinical trials. |
| Method of administration | 1. On the basis of routine GVHD prevention in the experimental group, UC-MSCs were reinfused 45 days after transplantation at a dose of $1 \times 10^6$ /kg per infusion; once every two weeks, a total of 4 times
2. Control group: routine GVHD prevention (Beijing program*) (MMF) 0.5g q12h -7d~90d, cyclosporine (CsA) 1.25mg/kg,; -1 day increment to 2.5mg/kg ; After the patient can tolerate orally, switch to 5 mg/kg orally, and the concentration is maintained at 200-300ng/ml; Slowly reduce the dose 180 days after transplantation; Methotrexate (MTX) 15mg/m  d1, 10mg/m  d3,6 ,11)                          |
| Observation period       | (1) Real-time observation of the occurrence of acute and chronic GVHD after transplantation;
(2) Follow-up: relapse, death and HSCT related complication                                                                                                                                                                                                                                                                                                                                                                                                                                                                                              |
| Primary Endpoint         | Severe chronic GVHD                                                                                                                                                                                                                                                                                                                                                                                                                                                                                                                                                                                                                                      |
| Secondary Endpoint       | Chronic GVHD, acute GVHD, Overall survival (OS), GVHD-free and Relapse-free survival (GRFS).                                                                                                                                                                                                                                                                                                                                                                                                                                                                                                                                                             |

|                   |                                                                                            |
|-------------------|--------------------------------------------------------------------------------------------|
| Safety evaluation | Incidence of adverse events (AE) and severe AE during 45 days to 100 days after haplo-HSCT |
| Study period      | 2016.4-2022.2                                                                              |

29

30

31

32  
33  
34  
35  
36  
37  
38  
39  
40  
41  
42  
43  
44  
45  
46  
47  
48  
49  
50  
51  
52

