### 240     **6.3.2 Hematopoietic stem cell mobilization, collection and reinfusion**

241     The donors were given subcutaneous injection of recombinant human granulocyte colony-stimulating  
242     factor ( rhGCSF ) at  $10\text{ u g}/\text{kg} / \text{d}$  for 4 days, and peripheral blood stem cells (peripheral blood stem  
243     cells) were collected by a German Fresenius blood cell separator on d5 . blood stem cells , PBSC) . On  
244     day 6 , bone marrow collection was performed. After epidural anesthesia was performed, the donor was  
245     placed prone on the operating bed, and puncture was performed at different depths and multiple sites on  
246     the bilateral iliac ridges for collection; if it is estimated that more than 600ml of bone marrow fluid  
247     needs to be collected, the donor should be adjusted to the supine position, collected in bilateral anterior  
248     superior iliac spine puncture. If the donor and recipient ABO blood type is incompatible on the primary  
249     side, erythrocytes are removed by hydroxyethyl starch sedimentation; if the secondary side is  
250     incompatible, the bone marrow fluid needs to be centrifuged at  $4^{\circ}\text{C}$  at a low temperature, and then the  
251     plasma in the bone marrow fluid is removed with a plasma separator.

252     **6.4 Prevention of GVHD after haploid hematopoietic stem cell transplantation**

253     (1) Experimental group: On the basis of conventional GVHD prevention, UC-MSCs were infused 45  
254     days after transplantation at a dose of  $1 \times 10^6/\text{kg}$  with the interval of 14 days for 4 times.

255     (2) Control group: Beijing program for routine GVHD prevention (MMF) 0.5g q12h -7d~90d,  
256     cyclosporine (CsA) 1.25mg/kg, continuous intravenous drip; -1 day increment to 2.5mg/kg; After the  
257     patient can tolerate oral administration, it is changed to oral 5 mg/kg, and the concentration is  
258     maintained at 200-300 ng/ml; the dose is slowly reduced 180 days after transplantation; methotrexate  
259     (MTX) 15 mg/m^2 d1, 10 mg/m^2 d3, 6,11)

260     **6.5 Indicator observation**

261     (1) The incidence of severe chronic GVHD

262     (2) The incidence of II-IV acute GVHD, the incidence of chronic GVHD, OS, Post-transplant patient  
263     GRFS (GVHD-free and relapse-free survival)

264     **6.6 Therapeutic Monitoring Protocol**

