265     After hematopoietic reconstruction to 1 year after transplantation, clinicians were blinded to the  
266     treatment allocation will access:

267     (1) Routine blood tests, liver and kidney function tests, CMV and EBV and other viral indicators (at  
268     least monthly)

269     (2) Bone marrow imaging, bone marrow biopsy (monthly)

270     (3) MRD, related gene mutation detection (monthly)7. Safety and Adverse Events

271     Safety will be measured and assessed daily by documenting potential adverse effects of treatment.  
272     Patients will be tested for potential toxicity that may arise from the treatment through tests such as  
273     medical history, physical examination, blood tests, etc.

274     **6.7 Recording of Adverse Events**

275     Investigators can gather information on adverse events through special questions or, in certain  
276     circumstances, tests in their interactions with each patient. All information about adverse events needs  
277     to be entered into the database immediately and into the Adverse Events module of the Case Report  
278     Form (CRF). All apparently relevant signs, symptoms, and abnormal diagnoses need to be entered into  
279     the database and grouped under the same diagnosis.

280     All adverse events that occurred during the study period were required to be recorded. All adverse  
281     events needed to be followed until resolved, stabilized, or until confirmed that study treatment or

282 participation was not an issue. Serious adverse events that persisted at the end of the study had to be  
283 followed until final results were determined. Any serious adverse events that occur after the study and  
284 that may be related to study treatment or study participation need to be recorded and reported promptly.  
285 If any subject has the following conditions within 2 weeks of receiving cell reinfusion therapy , the  
286 study will be required to be re-reviewed, and the clinical trial at this stage will be suspended:

- 287 (1) Respiratory failure requires artificial respirator.  
288 (2) Grade 4 (life-threatening) toxicity due to treatment regimen.  
289 (3) Death.

290

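### The only stated safety window ends at day 100; later adverse events and infections are recorded, but the SAP does not say whether they will be compared between arms

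*Combined protocol and SAP*

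**What the plan says.** The safety evaluation row of the synopsis reads "Incidence of adverse events (AE) and severe AE during 45 days to 100 days after haplo-HSCT". No other safety endpoint is given.

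For the experimental arm, the synopsis says "UC-MSCs were reinfused 45 days after transplantation at a dose of" the stated cell dose, "once every two weeks, a total of 4 times". Section 6.4 gives the same schedule as "with the interval of 14 days for 4 times".

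Collection is wider than the endpoint:

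- Section 6.7: "All adverse events that occurred during the study period were required to be recorded". Events are followed until they resolve or stabilise. "Any serious adverse events that occur after the study and" may be related to study treatment or participation must also be recorded and reported.
- Section 6.6: blood tests and CMV, EBV and other viral markers are checked no less than monthly, over a period given as "After hematopoietic reconstruction to 1 year after transplantation".

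A 2-week period after infusion appears once, in Section 6.7: "If any subject has the following conditions within 2 weeks of receiving cell reinfusion therapy". It introduces the conditions (ventilated respiratory failure, grade 4 toxicity from treatment, death) that suspend the trial for re-review.

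Section 11 compares adverse events between arms by Mann-Whitney, chi-squared and Fisher's exact tests. It gives no time window and lists no comparison of infections or viral reactivation. Section 2 makes safety part of the trial's purpose.

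**The concern.** The documents give three scopes for adverse events: day 45 to day 100 (synopsis), the whole study period (Section 6.7) and none stated (Section 11). If the synopsis governs, a non-fatal toxicity or infection after day 100 is recorded but plays no part in the safety conclusion. If Section 11 governs, the window is open and could be settled after the data are seen.

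This matters for an immunomodulatory product. Section 1.1 cites the centre's previous study as showing prevention of chronic GVHD without more infection, and says this trial will observe transplant complications and immune reconstitution. Routine cyclosporine is tapered only from day 180 (Section 6.4), so background immunosuppression continues well beyond the cut-off. A comparison confined to day 100 cannot show whether the infection claim holds later.

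The window is also anchored to transplant and not to the last infusion, and the documents give no tolerance for late infusions. Cover after the fourth infusion therefore depends on its being given on time.

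**Working it through.** The plan derives no figure for the window, so the check is calendar arithmetic followed by a comparison of sections.

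**Inputs.** First infusion day 45; 4 infusions; interval 14 days (synopsis; Section 6.4). Safety window day 45 to day 100 (synopsis). Two weeks after infusion = 14 days (Section 6.7, used here only as a yardstick). Monitoring to 1 year (Section 6.6), taken as day 365.

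**Nominal schedule.** Infusion day = 45 + 14 × (k − 1), k = 1 to 4: days 45, 59, 73, 87.

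**Length of the window.** 100 − 45 + 1 = 56 days = 4 × 14.

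**Cover after the fourth infusion, on schedule.**
- Infusion day counted as day 1: the blocks are days 45-58, 59-72, 73-86 and 87-100. All 14 days are covered.
- Infusion day counted as day 0: 14 days run to 87 + 14 = 101. Cover is 100 − 87 = 13 days, one day short.

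The documents do not say which convention applies.

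**Cover if the fourth infusion is x days late.** Days covered = 13 − x (day 0 convention) or 14 − x (day 1 convention), not below 0. The values of x are illustrative.

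| Delay x | Infusion 4 on day | Covered, day 0 convention | Covered, day 1 convention |
|---|---|---|---|
| 0 | 87 | 13 of 14 | 14 of 14 |
| 3 | 90 | 10 of 14 | 11 of 14 |
| 7 | 94 | 6 of 14 | 7 of 14 |
| 13 | 100 | 0 of 14 | 1 of 14 |
| 14 | 101 | infusion outside window | infusion outside window |

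**Time after day 100.** Day 45 to day 365 inclusive is 365 − 45 + 1 = 321 days. The stated window is 56/321 = 17% of that; 321 − 56 = 265 days of planned monitoring lie beyond it.

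**What is analysed after day 100.**

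| Item | Collected after day 100? | Comparison specified? |
|---|---|---|
| Death, relapse | Yes | Yes: OS, GRFS and relapse (Section 11) |
| Non-fatal adverse events | Yes (Section 6.7) | Not in the synopsis endpoint; Section 11 is silent on window |
| CMV, EBV, other viral markers | Yes, to 1 year (Section 6.6) | None named |
| Infections | Yes, as adverse events (Section 6.7) | None named |

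**The case against.** The case for leaving the plan alone has real force. The 56-day window equals four 14-day cycles, so it looks designed to match the infusion period. It is the same calendar window in both randomised arms, which is the cleaner comparison. Later events are recorded, possibly related serious events are reported even after the study, and fatal late infections count in OS. Section 11 does not impose a day-100 limit on the adverse-event tests. All of this stands. It leaves unanswered which window the SAP will use and whether late infections will be compared.

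Three stronger readings are tempting, and the documents do not support them.

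1. A reader might infer that the plan cuts off the fourth infusion's own observation window even with perfect timing. The shortfall is at most one day and vanishes if the infusion day counts as day 1. The 2 weeks in Section 6.7 is a suspension trigger, not an adverse-event observation window, and it operates whatever the synopsis window is.
2. A reader might infer a one-sided bias, with the omitted time belonging to the sickest treated patients. Only the MSC arm has infusions to delay, but the documents give no frequency, tolerance or reason for delay, and time after day 100 is omitted for controls too. What can be said is that a delay would lose MSC-exposed time.
3. A reader might infer that late toxicity is ignored. It is collected; it is missing only from the stated endpoint.

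**Conclusion.** The point holds as a gap in the stated safety analysis. On schedule the day-100 limit costs one day of cover after the fourth infusion at most, which is immaterial. With delay the loss is day for day: about half of the 14 days at a 7-day delay, and the infusion itself at 14 days. Those delays are assumptions.

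The more substantial part does not depend on delay. For 265 of the 321 days from day 45 to 1 year, non-fatal adverse events and infections fall outside the only stated safety endpoint, and Section 11 does not say whether they will be compared. The primary efficacy analysis is unaffected. The improvement is cheap and worth making because safety is a stated purpose and the data are already collected. It rests on reading 1 year as day 365 and on the synopsis row being the complete safety endpoint, since the documents give no other.

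**What to change.** Reconcile the synopsis safety row, Section 6.7 and Section 11:

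1. State the adverse-event window in Section 11, and the day-count convention.
2. Keep the day 45-100 table.
3. Add a between-arm comparison from day 45 to 1 year after transplant, over one common window for both arms, of severe/serious adverse events, grade 3 or higher infections, and CMV/EBV reactivation. Say whether severe, serious or both is meant, since the synopsis uses one term and Section 6.7 the other. Define reactivation, and say how infections are graded: the Section 3.4 table refers to CTCAE v4.0 but shows no infection row.
4. Because death shortens observation over the longer window, report these as cumulative incidences with death as a competing event; Section 11 already uses that approach for chronic GVHD.

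Do not tie the window to the date of the last infusion. That would make its length depend on treatment timing after randomisation in one arm only. Rates per person-time would not repair this if risk changes with time since transplant.

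The cost is SAP and synopsis wording and a few tables, with no new visits or tests. The downside is that late adverse-event and infection rates may look less favourable than the day 45-100 figures.

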## 53 1. Research background

### 54 1.1 Background Introduction

55 Allogeneic hematopoietic stem cell transplantation (allo-HSCT) is an effective method for the  
56 treatment of acute leukemia. HLA-matched sibling donors are the most ideal choice, but the chance of  
57 matching is only 25%, rather than consanguinity. The probability of matching donors is only 1 in  
58 50,000 to 100,000. HLA haploid hematopoietic stem cell transplantation (haplo-HSCT) effectively  
59 solves the problem of donor source. However, haploid transplantation that crosses the HLA barrier has  
60 a higher incidence of complications, of which graft versus host disease (GVHD) is the most important  
61 problem, and the incidence is significantly higher than that of HLA homozygous siblings  
62 Hematopoietic stem cell transplantation.

63 GVHD is a disease caused by immune cells ( mainly T cells ) contained in allografts that  
64 recognize the recipient's tissue antigens and launch an immune attack . It is the main complication of  
65 allo-HSCT and the main cause of death . According to the priority of onset, it is divided into acute  
66 GVHD (aGVHD: occurs within 100 days after transplantation ) and chronic GVHD (cGVHD: occurs  
67 after 100 days ). Acute GVHD has abrupt onset, rapid progression, and even life-threatening;  
68 chronic GVHD is prolonged and unhealed, seriously affecting the quality of life of patients. The  
69 treatment process of GVHD is long, the side effects of hormones or immunosuppressants are large, the  
70 incidence of severe infection is also significantly increased, and some patients have poor efficacy, so  
71 the prevention of GVHD is very important. At present, the prevention of GVHD is mainly to use  
72 immunosuppressive agents to remove lymphocytes in the transplant, but it also increases the recurrence  
73 of infection and leukemia, and the incidence of acute and chronic GVHD in haplo -HSCT patients is  
74 still as high as 50%; New methods for GVHD with high efficiency and low toxicity are of great  
75 significance.

76 Mesenchymal stromal cells (MSCs) are non-hematopoietic adult pluripotent stem cells first  
77 identified in the bone marrow stroma by Friedenstein in 1968. Studies have found that MSCs can  
78 maintain and increase the specific colony-forming units of CD34+ hematopoietic stem cells,  
79 participate in regulating the growth of hematopoietic cells , and also have unique immunoregulatory  
80 properties. MSCs express moderate amounts of human leucocyte antigen (human leucocyte antigen ,  
81 HLA ) class I molecules , do not express HLA class II molecules , nor do they express FAS ligands and  
82 co-stimulatory molecules , such as B7-1 , B7-2 , CD40L, which can inhibit the Proliferative responses

of T cells in mixed lymphocyte cultures ( MLCs ) or mitogen stimulation. Animal experiments have found that MSCs from HLA-matched donors or " third parties " derived from expanded in vitro can prolong the survival time of allogeneic implantation into the skin after infusion into animals  , confirming that MSCs can play an immunosuppressive role in vivo.

The incidence of II-IV grade aGVHD after haploid hematopoietic stem cell transplantation is generally about 50%  , while the incidence of aGVHD in the treatment of refractory and recurrent hematological malignancies is only 24% after haploid hematopoietic stem cell transplantation combined with infusion of umbilical cord mesenchymal cells , suggesting that MSC combined infusion can prevent the occurrence of aGVHD  . In addition, our center proved for the first time internationally that the 2-year cumulative incidence of chronic GVHD after haplo -HSCT followed by sequential infusion of umbilical cord mesenchymal stromal cells (UC - MSCs) was 27.4%, which was significantly lower than 49.0% of the control group (P=0.021), showing that UC -MSCs can prevent the occurrence of cGVHD without increasing infection and tumor recurrence after transplantation  . The current studies on the prevention of GVHD by MSCs are all clinical studies on the prevention of aGVHD or cGVHD by MSCs alone. Based on the previous research, we plan to adopt the strategy of co-transplantation of UC-MSCs and HSCs and phased application of MSCs after transplantation to establish a safe and effective scheme that can prevent both aGVHD and cGVHD, and preliminarily elucidate its mechanism.

With the support of grants from the National Key R&D Program of China (2022YFA1103300, 2022YFA1103304), we designed a multi-center, prospective, randomized, controlled clinical study, and invited well-known domestic hematopoietic stem cell transplantation experts to conduct multiple demonstrations and formulate a research plan. For haplo-HSCT patients, the fourth-generation UC-MSCs were used without any genetic modification or gene editing. On the basis of routine GVHD prevention, the experimental group, on the basis of routine GVHD prevention, was infused with UC-MSCs 4 5 days after transplantation at a dose of  $1 \times 10^6$ /kg per infusion; once every two weeks, a total of 4 times . To explore the efficacy of UC-MSCs in preventing GVHD after haplo-HSCT , observe the recurrence rate after transplantation, transplantation-related complications and immune reconstitution, and preliminarily explore the relevant mechanisms. Explore new clinical and practical techniques for the prevention of GVHD after haplo-HSCT .

113

114

